The M_2_ margin (relative efficacy of the experimental treatment to the active comparator) is based on a fraction retention factor (*f)* of the M_1_, given that the relative efficacy of the experimental treatment to the active comparator could only be larger than the efficacy with placebo if the active comparator is worse than placebo. The fraction retention varies according to the condition investigated: for instance, in studies focusing on vaccines and oncology, the *f* value should be close to 1; whereas for chronic and functional disorders, this value ranges between one-half and one-third.^31^^,^^79^ There is no consensus regarding the *f* value in non-inferiority trials for MDD, although Nutt et al.^81^ proposed that for generalized anxiety disorder, the value should be 50%. In this trial, we adopted the *f* value of 50%, based on Nutt et al.^81^ and considering that MDD is comparable to generalized anxiety disorder with regard to methodological aspects (large placebo response, short duration of clinical trials, similar pharmacological treatments, comparable scales etc.).

Therefore, in our trial, M_2_/M_1_ = 0.5, although M_1_ is based on the difference between the active comparator and placebo and it will be known only when the study has been finished. Although this approach indexes the relative efficacy of tDCS versus escitalopram according to the placebo response of the study, it is theoretically possible that the escitalopram-placebo difference is too large, thus producing a large M_2_ value that could favor a finding that comparison between escitalopram and tDCS does not show any significant difference, even if escitalopram clinically outperforms tDCS. To avoid this issue, we will only consider that tDCS was non-inferior to escitalopram if the mean difference between escitalopram and tDCS is less than 3 points on the HDRS-17. The threshold of 3 points was chosen considering the National Institute for Health and Clinical Excellence (NICE) guidelines, which establish that this is a clinically meaningful difference in efficacy.^82^

To determine the sample size, we first needed to establish the randomization proportions between the groups. Pigeot et al.^31^ recommended a 1:1:k_p_ ratio, where k_p_ is determined according to the fraction retention factor, as shown below:

$$k_{placebo}\;=\;\left[(1\;-\;f)\;\surd 2\;+\;2f\right]/(1\;+\;f^{2})$$

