According to this formula, for *f* = 0.5, k_p_ is 0.69. Therefore the optimal proportion for allocation between the groups is 1:1:0.69, or approximately 3:3:2, as used in ELECT-TDCS.

We estimated our sample size in accordance with the suggestion of Pigeot et al.^31^ for non-inferiority, triple-arm trials:

$$N_{arm}\geq {\left(t_{1-\alpha ,\;3n-3}\;+\;t_{1-\beta ,\;3n-3}\right)}^{2}*(1+f^{2}+{\left(1-f\right)}^{2})\;{*\left[\left(\sigma /\;{µ}_{DRUG}-{µ}_{PLACEBO})/(r-f\right)\right]}^{2*}$$

This formula shows that the sample size is a product of three factors (in parentheses). The factor in the first parentheses take into account the values of α and β, which were, respectively 0.025 (one-tailed) and 0.2. The factor in the second parentheses is the *f* value (the higher the *f* value is, the larger the necessary sample size will be), which was determined as 0.5 for our study. The factor in the last parentheses involves the standard deviation and effect sizes of the interventions. We took the value of the standard deviation to be a function of the difference in efficacy between the active comparator and the placebo:^31^

$$\sigma =\varepsilon \;({µ}_{DRUG}-{µ}_{PLACEBO})$$

The ε value indicates that the standard deviation is associated with the mean difference values observed in the study. It ranges from 0.2 to 2, and values > 1 are considered conservative. In the present study, we took the ε value to be 1.5, i.e. the standard deviation would be 1.5 times the value of the difference in efficacy between the active intervention and the placebo, which is compatible with depression studies in which the variance is usually high.^†^

Therefore, considering an attrition rate of 13% (similar to SELECT-TDCS), β = 0.2, α_one-tailed_ = 0.025, *f* = 0.5 and ε = 1.5, a total sample of 240 patients will be necessary in order to reject our null hypothesis. For 3:3:2 randomization, this means that in the end, 90, 90 and 60 patients will be respectively allocated to the tDCS, escitalopram and placebo groups.

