### Statistical analysis

In accordance with the recommendations of Pigeot et al.^31^ and Rothmann et al.,^79^ we use a modified *t* test to address our primary study hypothesis (i.e. that tDCS is non-inferior to escitalopram). A *t* test involves obtaining a T value, which should be higher than (in a one-tailed test, as in our study) or different to (in a two-tailed test) a critical *t* value. The T value is obtained by dividing the difference in the means by the mean error (obtained according to the variance and sample size). For this analysis, the T value will be obtained as follows:

$$T=({µ}_{tDCS}-0.5{µ}_{PLACEBO}-0.5{µ}_{DRUG})/\sigma \surd (1/n_{TDCS}+0.25/n_{DRUG}+0.25/n_{PLACEBO})$$

or

$$T=7.44({µ}_{tDCS}-0.5{µ}_{PLACEBO}-0.5{µ}_{DRUG})/\sigma (considering\;that\;the\;n\;values\;are\;known)$$

This T value should be higher than the critical *t*, which for a one tailed α of 0.025 and 237 (N-3) degrees of freedom would be 1.97.

We will also perform exploratory analyses to identify whether a significant difference between the groups is observed over time. Therefore, we will perform mixed-model analyses of variance (ANOVAs) with one independent, within-subject variable (time, with three levels: baseline, week 3 and endpoint) and one independent, between-subject variable (group, with three levels). The dependent variables will be the scores from HDRS, MADRS or BDI. To determine whether a statistical significance is observed at a two-tailed p value of 0.05 or less, post-hoc analyses will be performed to analyze the main and interaction effects of our interventions. Exploratory analyses will also be performed to identify the influence of clinical, demographic and biological variables on the outcome. In addition, logistic regressions will be performed using response or remission as dependent variables and the group as an independent variable. Adverse effects will be assessed by counting the number of events in each group at each evaluation time. The chi-square test will be used to compare the frequency of adverse effects between the treatment groups.

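### The sample-size formula uses the equal-arms variance factor 1.5 where the 3:3:2 test carries 1.625; the sample-size line should be restated, and with r = 1 neither factor leads to 240

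*Protocol article*

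**What the plan says.** All of this is in the Protocol article, Methods.

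- **Allocation** (Design and sample size determination). The ratio is restricted to 1:1:k, with k set by the retention fraction f. "According to this formula, for *f* = 0.5, k_p_ is 0.69", and from this the article concludes that "the optimal proportion for allocation between the groups is 1:1:0.69, or approximately 3:3:2, as used in ELECT-TDCS".
- **Sample size** (same section). The per-arm size is (t₁₋α + t₁₋β)² × (1 + f² + (1−f)²) × [ε/(r−f)]², once σ is replaced by ε times the drug–placebo difference. The degrees of freedom are 3n−3. Alpha and beta are given as values "which were, respectively 0.025 (one-tailed) and 0.2", f is 0.5, and "we took the ε value to be 1.5". No value of r appears in the text at hand. After 13% attrition, "a total sample of 240 patients will be necessary in order to reject our null hypothesis", split 90/90/60.
- **Test** (Statistical analysis). The standard error of the primary contrast is σ√(1/n_tDCS + 0.25/n_drug + 0.25/n_placebo). This is reduced to a multiplier of 7.44 with 237 degrees of freedom.

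**The concern.** The sample-size formula has no k. Its factor 1.5 and its 3n−3 degrees of freedom belong to three equal arms, yet the trial randomises 3:3:2 and the planned test uses the unequal arm sizes. The calculation and the test it is meant to size therefore rest on different variances.

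What is at stake is whether the sample-size line can be reproduced and whether 240 patients give the 80% power that beta = 0.2 implies. A smaller matter is whether 0.69 is the optimum for this contrast, since k is the only stated basis for the randomisation ratio.

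**Working it through.** **Inputs.** From the article: f = 0.5; one-sided alpha 0.025; beta 0.2; ε = 1.5; attrition 13%; arms 90/90/60, so k = 60/90 = 2/3. Assumed: r = 1, meaning tDCS truly equals escitalopram. Then [ε/(r−f)]² = (1.5/0.5)² = 9.

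**1. Reproduce the article's own figures.**
- Test multiplier: 1/√(1/90 + 0.25/90 + 0.25/60) = 7.442, as stated (7.44).
- Critical t at 237 degrees of freedom: 1.970, as stated (1.97).
- k: (1−f)√(2+2f)/(1+f²) = 0.5 × √3/1.25 = 0.693, as stated (0.69).

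**2. Compare the two variance factors.**
- Sample-size formula: 1 + 0.25 + 0.25 = 1.5.
- 3:3:2 design: 1 + 0.25 + 0.25/(2/3) = 1.625.
- √(90/1.625) = 7.44, the printed multiplier; √(90/1.5) = 7.75. The test therefore carries 1.625.
- Degrees of freedom differ in the same way: 3n−3 at n = 90 is 267, while the test uses 240 − 3 = 237.

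**3. Sample size at the stated inputs** (t quantiles, iterated; attrition applied as N/0.87).

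| Factor used | n per active arm | Evaluable total | With attrition |
|---|---|---|---|
| 1.5, equal arms | 106.6 | 320 | 368 |
| 1.5, its n kept for the active arms at 3:3:2 | 106.6 | 284 | 327 |
| 1.625, 3:3:2 | 115.5 | 308 | 354 |

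No row gives 240.

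**4. Power at the planned size** (noncentral t, one-sided 0.025, r = 1).
- 90/90/60: noncentrality 7.442 × 0.5/1.5 = 2.481; power 69.5%.
- After 13% attrition (78.3/78.3/52.2): noncentrality 6.942 × 0.5/1.5 = 2.314; power 63.4%.
- 240 in equal arms: power 67.9%.

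**5. Range for the unstated r.** The required size scales approximately with 1/(r−0.5)².
- r = 0.9: 308 × (0.5/0.4)² ≈ 481 evaluable.
- r = 1.1: 308 × (0.5/0.6)² ≈ 214 evaluable, or about 246 with attrition.
- 240 including 13% attrition needs r of about 1.11, or ε of about 1.23 with r = 1.
- A total near 240 (242.7) also appears with one-sided alpha 0.05, k = 2/3 and no attrition allowance. The article does not say that this was done.

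**6. Optimal k under 1:1:k.** Total N is proportional to (2+k)(1.25 + 0.25/k) = 2.75 + 1.25k + 0.5/k. Setting the derivative to zero gives k² = 0.5/1.25 = 0.4, so k = 0.632. This equals (1−f)√(2+2f²)/(1+f²).
- Total-N factors: 4.3311 at 0.632; 4.3333 at 2/3 (+0.05%); 4.3371 at 0.69 (+0.14%).

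**The case against.** **The equal-arms factor may be harmless.** If the formula gives a total that is then split 3:3:2, the equal-arms form is conservative: 3 × 1.5 = 4.5 against (8/3) × 1.625 = 4.333, an excess of 3.8%. This stands. The 8.3% increase in active-arm size (1.625/1.5) applies only if the balanced per-arm n is kept while placebo is reduced, and the article does not say which route was taken. It would therefore be wrong to report a flat 8.3% understatement. The mismatch between formula and test remains on either route.

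**The test itself is right.** This also stands. The multiplier 7.44 handles the unequal arms correctly, so the error is confined to the planning formula.

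A reader might also infer three stronger things:
- *The k formula evaluates to 1.37, so following it would give a clearly worse allocation.* That requires the radical to cover only the 2. The extracted text does not mark its extent, and √(2+2f) gives exactly the stated 0.69.
- *2:1:1 would be better.* For this one contrast its factor is 4.0 against 4.333. But the article restricts itself to 1:1:k and assigns the comparator and placebo arms direct comparisons of their own. At 240 patients, 2:1:1 would raise the drug–placebo variance term from 1/90 + 1/60 = 0.0278 to 1/60 + 1/60 = 0.0333.
- *The missing k explains why 240 is too small.* It does not: the k-free formula asks for 320 evaluable patients with equal arms, more than the corrected 308.

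**Conclusion.** The point holds in a limited form. The sample-size formula uses 1.5 where the 3:3:2 design and the planned test use 1.625. This is an internal contradiction, visible in the article's own 7.44.

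With the corrected factor, about 308 evaluable patients are needed (about 354 with attrition). The planned 240 has about 70% power, or about 63% after attrition. These figures assume r = 1, dropouts that contribute no information, and the retention test alone without the additional 3-point condition. The gap to 80% is not caused by the missing k. The article's stated inputs do not lead to 240 with either factor unless r, ε, alpha or the attrition allowance differs from what is stated or assumed here.

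The k value is a minor matter. 0.69 corresponds to √(2+2f), whereas the plan's variance implies √(2+2f²), or 0.63. A lost square would explain this, but the cited source is not available to confirm it. The ratio in use lies between the two values and costs 0.05% in total N.

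**What to change.** 1. In the sample-size formula, replace (1−f)² by (1−f)²/k with k = 2/3, and replace 3n−3 by N−3.
2. State r, then restate the sample-size line from the corrected formula: about 115.5 evaluable per active arm, 308 in total and about 354 with 13% attrition if r = 1.
3. State the power that 240 provides (about 70%, or about 63% after attrition, with r = 1). If another r, ε, alpha or attrition rule was used to reach 240, give it and show that it reproduces the figure.
4. Give k as (1−f)√(2+2f²)/(1+f²) = 0.63, and describe 3:3:2 as near-optimal among 1:1:k designs.

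The cost is a text correction and a short recalculation. The randomisation ratio and the planned test stay as they are. Whether the restated power calls for a different total is a separate decision that this correction does not settle.

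### The 240 patients give 80% power only if tDCS is truly better than escitalopram; at equal efficacy the listed inputs give about 70%, and the ratio r that decides this has no stated value

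*Protocol article*

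**What the plan says.** The section Design and sample size determination in the protocol article gives a formula for the number per arm. It has three factors: the alpha and beta quantiles; a term in f; and the squared ratio of the standard deviation to the escitalopram–placebo difference, divided by (r − f).

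- Alpha and beta: "which were, respectively 0.025 (one-tailed) and 0.2".
- Retention fraction: f = 0.5.
- Spread: "we took the ε value to be 1.5", meaning that "the standard deviation would be 1.5 times the value of the difference in efficacy between the active intervention and the placebo".
- Dropout: "considering an attrition rate of 13% (similar to SELECT-TDCS").
- Result: "a total sample of 240 patients will be necessary in order to reject our null hypothesis", allocated 3:3:2 as 90 tDCS, 90 escitalopram and 60 placebo.

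The section Statistical analysis gives the primary test. It is a T statistic with multiplier 7.44, and its critical value "for a one tailed α of 0.025 and 237 (N-3) degrees of freedom would be 1.97".

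The symbol r appears in the formula, but the text shown neither defines it nor gives it a value.

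**The concern.** The sentence that derives 240 reads as a complete list of inputs, but one quantity in the formula is missing from it, and the answer depends heavily on that quantity. The usual planning value for a non-inferiority trial is equal true efficacy. At that value the listed inputs do not lead to 240.

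What is at stake is the type II error of the single primary hypothesis. If the trial was planned at equal efficacy, the chance of missing true non-inferiority is nearer 30% than the stated 20%. A failed primary test could then be read as evidence against tDCS when the sample was small for its own assumptions. If it was planned on tDCS being better than escitalopram, readers need to know that the 80% depends on that.

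**Working it through.** **Inputs from the article.** One-sided alpha 0.025; beta 0.2; f = 0.5; ε = σ/(µ_drug − µ_placebo) = 1.5; allocation 90/90/60; attrition 13%.

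**Input not in the text shown.** r = (µ_tDCS − µ_placebo)/(µ_drug − µ_placebo). This is the reading that fits the hypotheses as written. I assume r = 1 and show a range.

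**1. Reproduce the article's own test constants.**
- Multiplier: 1/√(1/90 + 0.25/90 + 0.25/60) = 7.442. The article gives 7.44.
- One-sided 0.025 critical t on 237 degrees of freedom: 1.970. The article gives 1.97.

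Both agree. They confirm one-sided 0.025 and a multiplier based on all 240 patients.

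**2. Sample size at r = 1.**
- (1.960 + 0.842)² = 7.849.
- Formula as printed, equal arms: 7.849 × (1 + 0.25 + 0.25) × (1.5/0.5)² = 7.849 × 1.5 × 9 = 106.0 per arm, or 318 in total before attrition.
- With 3:3:2 allocation the placebo term becomes 0.25/(2/3) = 0.375, so the middle factor is 1.625. Then 7.849 × 1.625 × 9 = 114.8 per active arm, and × 8/3 = 306 evaluable. Dividing by 0.87 gives 352 randomised.
- The noncentral t distribution gives 309 evaluable and 355 randomised, rounded up.

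The figure of 240 is not reproduced at r = 1.

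**3. Power of the stated test with 240 patients.** The numerator of T equals (r − 0.5)(µ_drug − µ_placebo), and σ = 1.5(µ_drug − µ_placebo). The noncentrality is therefore 7.442 × (r − 0.5)/1.5.
- r = 1, all 240: 7.442 × 0.5/1.5 = 2.481 against 1.970. Power is 69.5%.
- r = 1, 13% lost (78.3/78.3/52.2, about 209): the multiplier is 6.94 and the noncentrality 2.314. Power is 63.4%.

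**4. Dependence on r** (ε = 1.5, one-sided 0.025, noncentral t):

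| r | 240 analysed | about 209 analysed |
|---|---|---|
| 0.90 | 51% | 45% |
| 0.95 | 60% | 54% |
| 1.00 | 70% | 63% |
| 1.05 | 78% | 72% |
| 1.10 | 84% | 79% |

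Power reaches 80% at r of about 1.07 with 240 patients and about 1.11 with 209.

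**5. Dependence on ε** (r = 1):

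| ε | 240 analysed | about 209 analysed |
|---|---|---|
| 1.00 | 96% | 93% |
| 1.25 | 84% | 79% |
| 1.50 | 70% | 63% |
| 2.00 | 46% | 41% |
| 2.50 | 32% | 28% |

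**6. Which settings give about 240?**
- Stated alpha, 13% attrition and r = 1.1: 7.849 × 1.625 × (1.5/0.6)² = 79.7 per active arm, or 212.6 in total. Multiplying by 1.13 gives 240; dividing by 0.87 gives 244.
- r = 1, one-sided alpha 0.05 and no attrition: 6.183 × 1.625 × 9 × 8/3 = 241, with 79.6% power on 240. This contradicts both the stated alpha and the stated attrition allowance.

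**The case against.** The strongest reply is that r = 1 is the reviewer's value and not the article's. The formula carries an asterisk and the ε sentence a dagger, and the text of those notes is not in the copy at hand, so r may be given there. With r = 1.1, every stated input is compatible with 240. The introduction also offers some support for r above 1: in the earlier trial tDCS was superior at endpoint while sertraline was not superior to placebo. However, it adds that tDCS and sertraline did not differ significantly. This reply stands to the extent that the 70% and 63% figures are conditional on r = 1.

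Three stronger readings are tempting, and the document does not support them.

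- A reader might infer that the article's inputs by themselves prove 70% power and a type II error of 30% to 37%. They do not, because r is not among the inputs shown.
- A reader might infer that the authors calculated with one-sided alpha 0.05. That is one of two settings that return about 240, and the critical value of 1.97 in the analysis section fits 0.025.
- A reader might take 63% as the power of the main analysis. That analysis is intention-to-treat, which the article describes as imputing data for drop-outs, and it uses 237 degrees of freedom. The 63% describes an analysis of about 209 patients with data, such as the per-protocol confirmation.

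The reply does not remove the point. The sentence deriving 240 leaves out a value on which the result turns. Elsewhere the design section describes the result sought as the two treatments being truly equivalent, which makes r = 1 the natural planning case.

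**Conclusion.** The point holds in conditional form. At r = 1, the stated alpha, beta, f, ε and allocation need about 306 to 309 evaluable patients. The 240 are short by about 66 to 69 evaluable patients, or about 112 to 115 randomised after 13% attrition. Power is then about 70% with all 240 analysed and about 63% on 209.

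At the stated alpha and ε, the 80% claim holds only if tDCS is truly better than escitalopram, by about 7% of the escitalopram–placebo effect without attrition or about 11% with it. Whichever r was used, the article as it stands does not let a reader see what the 80% depends on.

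The figures assume a common standard deviation and the T statistic as printed. They leave out the additional 3-point condition on the HDRS-17, which can only lower the chance of declaring non-inferiority.

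**What to change.** In the section Design and sample size determination:

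1. Define r, state the value used, and show how 240 follows from it, including how the 13% attrition enters.
2. Report that at r = 1, with ε = 1.5 and one-sided alpha 0.025, 240 patients give about 70% power (about 63% if about 209 contribute data).
3. Add a short power table over r and ε, such as the two shown above.
4. If the 80% rests on r of about 1.1, say explicitly that tDCS was assumed better than escitalopram, and give the reason.

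This changes wording only. It adds no patients and leaves the test, the margin and alpha as they are. The cost is a less favourable stated power at equal efficacy.

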### Statistical analysis

In accordance with the recommendations of Pigeot et al.^31^ and Rothmann et al.,^79^ we use a modified *t* test to address our primary study hypothesis (i.e. that tDCS is non-inferior to escitalopram). A *t* test involves obtaining a T value, which should be higher than (in a one-tailed test, as in our study) or different to (in a two-tailed test) a critical *t* value. The T value is obtained by dividing the difference in the means by the mean error (obtained according to the variance and sample size). For this analysis, the T value will be obtained as follows:

$$T=({µ}_{tDCS}-0.5{µ}_{PLACEBO}-0.5{µ}_{DRUG})/\sigma \surd (1/n_{TDCS}+0.25/n_{DRUG}+0.25/n_{PLACEBO})$$

or

$$T=7.44({µ}_{tDCS}-0.5{µ}_{PLACEBO}-0.5{µ}_{DRUG})/\sigma (considering\;that\;the\;n\;values\;are\;known)$$

This T value should be higher than the critical *t*, which for a one tailed α of 0.025 and 237 (N-3) degrees of freedom would be 1.97.

We will also perform exploratory analyses to identify whether a significant difference between the groups is observed over time. Therefore, we will perform mixed-model analyses of variance (ANOVAs) with one independent, within-subject variable (time, with three levels: baseline, week 3 and endpoint) and one independent, between-subject variable (group, with three levels). The dependent variables will be the scores from HDRS, MADRS or BDI. To determine whether a statistical significance is observed at a two-tailed p value of 0.05 or less, post-hoc analyses will be performed to analyze the main and interaction effects of our interventions. Exploratory analyses will also be performed to identify the influence of clinical, demographic and biological variables on the outcome. In addition, logistic regressions will be performed using response or remission as dependent variables and the group as an independent variable. Adverse effects will be assessed by counting the number of events in each group at each evaluation time. The chi-square test will be used to compare the frequency of adverse effects between the treatment groups.

For non-inferiority trials, it is unclear which approach (intention-to-treat, ITT; or per protocol, PP) should be used. ITT imputes data from study drop-outs and, although conservative for superiority trials, it can favor the hypothesis of lack of difference between groups in a non-inferiority design and, therefore, benefit (instead of penalizing) a non-inferiority design with methodological flaws. Nonetheless, neither the FDA^83^ nor the EMA^84^ clearly recommend the optimal approach and they suggest that both ITT and PP should be used. Mulla et al.^85^ also suggested that ITT should be used because it has the additional benefit of being more robust in relation to bias, compared with PP analysis. Therefore, missing data will be handled using an ITT approach and the findings will be confirmed through PP analysis. Finally, we will perform additional analyses according to the patients’ adherence to the study, using the categories of “fully adherent sample” (patients who missed or rescheduled two visits or fewer) and “completer sample” (patients who completed the study in accordance with the protocol). This approach was also used by George et al.^6^

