## METHODS

### Overview

The ELECT-TDCS trial randomizes patients into: sham-tDCS/placebo-pill (placebo group), sham-tDCS/escitalopram (escitalopram group) and active-tDCS/placebo-pill (tDCS group). It was approved by the Local and National Ethics Committee (CAAE:10173712.3.0000.0076) of the University Hospital and Clinics Hospital of the University of São Paulo and is registered in clinicaltrials.gov (NCT01894815). All study participants provide written, informed consent for participation in the study.

Our null hypothesis is that the improvement, i.e. the difference in efficacy between baseline and endpoint measurements of the tDCS group (µ_tDCS_) will be less than or equal to 50% (retention fraction *f* ≤ 50%) of the difference in the improvement between escitalopram and placebo (µ_drug_ - µ_placebo_). The study’s primary aim is to prove the alternative hypothesis, i.e. that this difference is greater than 50% (*f* > 50%).

$$H_{o}:\;{µ}_{tDCS}\;-\;{µ}_{placebo}\;\leq \;50\%\;({µ}_{drug}\;-\;{µ}_{placebo})$$

*or*

$$H_{o}:\;{µ}_{tDCS}\;-\;0.5\;{µ}_{placebo}\;-\;0.5\;{µ}_{drug}\;\leq \;0$$

$$H_{A}:\;{µ}_{tDCS}\;-\;{µ}_{placebo}>\;50\%\;({µ}_{drug}\;-\;{µ}_{placebo})$$

*or*

$$H_{A}:\;{µ}_{tDCS}\;-\;0.5\;{µ}_{placebo}\;-\;0.5\;{µ}_{drug}>\;0$$

In a non-inferiority triple-arm trial, there are three relevant comparisons: (1) experimental treatment versus active comparator (i.e. tDCS versus escitalopram); (2) experimental treatment versus placebo; and (3) active comparator versus placebo. Authors such as Koch and Röhmel^29^ have considered that the third comparison is not strictly necessary if the former two were significant, but in their approach, two or three null hypotheses would have to be independently rejected (thereby decreasing the P value), or the trial would only be valid if all hypotheses were rejected.^30^ Therefore, we use here an alternative model presented by Pigeot et al.^31^ and already used in the literature,^32^ in which the study aim can be presented in a single H_0_, which simultaneously tests the non-inferiority between active treatments and their superiority against placebo, thereby decreasing the number of multiple comparisons.

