Our study protocol was designed by drawing on our experience from our earlier SELECT-TDCS trial and other advances observed in the field. The choice of using escitalopram at a dose of 20 mg/day represents an advance over the 50 mg/day dose of sertraline used in SELECT-TDCS. The decision to increase the total number of sessions from 12 to 22 was based on findings from a meta-analysis^24^ that suggested that a higher tDCS “dose” would be associated with a larger improvement in depression. Other changes in relation to SELECT-TDCS include: a longer wash-out period to ensure that the subjects were truly “antidepressant drug-free”; an increase in the maximum age of participants in order to improve recruitment; use of automated tDCS devices for sham stimulation, so as to improve blinding; a longer study duration to address the effects of tDCS over a longer time frame; and use of HDRS-17 (instead of MADRS) as the primary outcome measurement, given that in SELECT-TDCS, HDRS-17 presented lower variance and greater psychometric validity (Cronbach’s alpha and intraclass correlation) than MADRS, and was also more sensitive towards detecting between-group differences (data not published).

Nonetheless, most aspects of the SELECT-TDCS trial were maintained, such as recruitment of unipolar depressed patients with different degrees of refractoriness in an acute episode of at least moderate severity; enrollment of antidepressant-free patients; inclusion of patients using benzodiazepine drugs, since we considered that exclusion of these patients could harm recruitment and, in fact, be ineffective given that participants can retain information regarding use of these drugs; bilateral (left-right) DLPFC stimulation; and comparison with a placebo arm, which is crucial, given that as the efficacy of active versus sham tDCS is still under investigation.

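### The primary T test compares unadjusted HDRS-17 changes; adjusting the same contrast for baseline HDRS-17 would cost one degree of freedom and could recover some precision

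*Protocol article*

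**What the plan says.** The Overview defines improvement as "the difference in efficacy between baseline and endpoint measurements of the tDCS group" (and likewise for the other arms) and states the null hypothesis on the three group means. The Discussion names the scale: "use of HDRS-17 (instead of MADRS) as the primary outcome measurement".

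The Statistical analysis section then fixes the test as a modified t "test to address our primary study hypothesis (i.e. that tDCS is non-inferior to escitalopram"), and describes its construction: "The T value is obtained by dividing the difference in the means by the mean error (obtained according to the variance and sample size"). The printed formula is the tDCS mean minus half the placebo mean minus half the escitalopram mean, divided by sigma times the square root of (1/n for tDCS + 0.25/n for escitalopram + 0.25/n for placebo). The critical value is that for "237 (N-3) degrees of freedom would be 1.97".

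The section Design and sample size determination adds a second condition: non-inferiority is accepted only if the mean difference between escitalopram and tDCS is below 3 HDRS-17 points.

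No covariate enters either part of this decision rule. The influence of clinical, demographic and biological variables is examined only in exploratory analyses.

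**The concern.** Baseline HDRS-17 is available for every patient, because a score of at least 17 is an entry criterion. A comparison of raw changes subtracts the whole baseline score, which amounts to assuming that endpoint rises one point for each baseline point. If the true slope b differs from 1, two things follow.

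- The SD of change is larger than the residual SD after adjustment, so the standard error of the contrast is larger than it needs to be.
- A chance baseline difference D between arms shifts the difference in mean endpoint-minus-baseline change by (b - 1) x D. That shift enters the T statistic. It also enters the 3-point condition, which as written compares a mean difference with a fixed threshold and has no interval around it.

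The placebo arm has only 60 patients, and on the plan's stated inputs (with equal efficacy of the two active arms assumed) power is below the 80% target. Precision is therefore worth having.

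The article settles this point rather than leaving it to an unseen analysis plan. N-3 degrees of freedom correspond to three means and no covariate, so a later plan that added baseline would change the stated statistic and its degrees of freedom.

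**Working it through.** **Inputs from the article.** One-sided alpha and beta "which were, respectively 0.025 (one-tailed) and 0.2"; retention fraction f = 0.5; epsilon = SD / (drug - placebo difference) = 1.5; arms of 90, 90 and 60; attrition 13%.

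**Inputs assumed.**
- r = 1, meaning equal true efficacy of tDCS and escitalopram relative to placebo. r appears in the sample-size formula without a value.
- Epsilon refers to the SD of change, the sigma of the T statistic.
- rho is the baseline-endpoint correlation and k is baseline SD / endpoint SD. The article gives neither.
- The slope of endpoint on baseline is common to the three arms.

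**1. Reproduce the plan's own figures.** 1 / sqrt(1/90 + 0.25/90 + 0.25/60) = 7.442, against the stated 7.44. The upper 2.5% point of t on 237 df is 1.970, against the stated 1.97. Both agree, so the unadjusted reading of the test is the right one.

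**2. Power of the unadjusted test.** Noncentrality = (r - f)/epsilon x 7.442 = (0.5/1.5) x 7.442 = 2.481. From the noncentral t on 237 df, power is **69.5%** with all 240 analysed. With 13% lost (78.3, 78.3 and 52.2 per arm), power is **63.4%**.

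**3. Variance after adjustment.** Take the endpoint SD as 1.
- Var(change) = k² + 1 - 2 rho k
- Var(ANCOVA residual) = 1 - rho²
- Ratio v = (1 - rho²) / (k² + 1 - 2 rho k)

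When k = 1 this reduces to (1 + rho)/2. It equals 1, meaning no gain, when the slope rho/k is 1.

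**4. Power after adjustment.** Noncentrality becomes 2.481 / sqrt(v), with N-4 df.

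| k | rho | v | Power, N = 240 | Power after 13% loss |
|---|---|---|---|---|
| 0.7 | 0.2 | 0.96/1.21 = 0.793 | 79.2% | 73.4% |
| 0.6 | 0.3 | 0.91/1.00 = 0.910 | 73.6% | 67.5% |
| 0.5 | 0.4 | 0.84/0.85 = 0.988 | 70.0% | 63.9% |
| 0.5 | 0.5 | 1.000 (slope 1) | 69.5% | 63.4% |
| 1 | 0.2 | 0.600 | 89.1% | 84.5% |
| 1 | 0.4 | 0.700 | 84.0% | 78.6% |
| 1 | 0.6 | 0.800 | 78.9% | 73.1% |

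The entry cut of 17 narrows the baseline distribution, so the rows with k below 1 deserve at least as much weight as those with k = 1.

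**5. What 80% would need.** v must be about 0.775 with all 240 analysed, or about 0.675 after attrition. None of the k = 0.5 to 0.7 rows reaches either value.

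**The case against.** The strongest reply is that nothing here is wrong. Under randomisation the contrast of mean changes is unbiased and keeps its type I error, and it is the statistic on which the sample size was built. That stands: the point concerns efficiency only. The gain may also be close to nil, since it depends on two quantities the article does not give and the entry cut pushes towards the small end. That stands too, which is why the range matters more than any single figure.

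A reader might infer several stronger points that the article does not support.

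- *Adjustment can never lose precision.* This needs similar slopes across arms. The variance of this contrast is minimised by weighting the arm slopes by c²/n, about 0.62 for tDCS, 0.15 for escitalopram and 0.23 for placebo. A pooled slope (with equal baseline variance) weights them 0.375, 0.375 and 0.25. With assumed slopes of 1.2, 0.5 and 0.5, the best value is about 0.93 and the pooled slope about 0.76, so the change score's fixed 1 is closer.
- *Regression to the mean after the entry cut biases the result.* It acts equally in expectation on all randomised arms, and the coefficients 1, -0.5 and -0.5 sum to zero, so it cancels.
- *The exploratory ANOVA is faulty because baseline is a level of* "time, with three levels: baseline, week 3 and endpoint". Only the group main effect is diluted. The group-by-time interaction, which the article also plans to examine, answers the question about change over time.
- *The secondary models are faulty because* "logistic regressions will be performed using response or remission as dependent variables and the group as an independent variable". Response is already defined relative to baseline. In logistic regression a covariate changes the odds ratio from marginal to conditional, and covariates for secondary models are commonly left to the analysis plan.

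**Conclusion.** The point holds for the primary contrast and the 3-point condition, as avoidable loss of efficiency and avoidable exposure to chance baseline imbalance. It is not a finding of bias or of inflated type I error.

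Given r = 1 and a common slope, the variance saving is 1 to 21% for k = 0.5 to 0.7 with rho = 0.2 to 0.4, and 20 to 40% for k = 1 with rho = 0.2 to 0.6. It is zero at a slope of 1. With all 240 analysed, power moves from 69.5% to 70-79% in the first case and 79-89% in the second.

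It would be tempting to present adjustment as the cure for the power shortfall. The figures do not support that. The gap between 69.5% (or 63.4% after attrition) and the stated 80% is a separate sample-size question. It itself depends on r: a value of about 1.07 with all 240 analysed, or 1.11 after attrition, would close it without any adjustment.

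**What to change.** Before unblinding, amend the primary analysis as follows.

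- Keep the hypothesis, the retention fraction and the contrast (1, -0.5, -0.5).
- Estimate the contrast from an ANCOVA of endpoint HDRS-17 (or change) on group plus baseline HDRS-17. Use the model's residual SD and covariance matrix for the standard error, with N-4 degrees of freedom. If endpoint is the outcome, reverse the sign so that larger values still mean improvement. Endpoint and change give the same adjusted contrast.
- Apply the 3-point condition to the baseline-adjusted difference between escitalopram and tDCS.
- Keep the unadjusted T as a sensitivity analysis, so that the result stays traceable to the published plan.

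The cost is a change of wording and one degree of freedom (236 instead of 237 with all 240 analysed). No new data or patients are needed.
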